### Randomization, allocation, and blinding

2.8

The central randomization method will be performed by the Chengdu University of Traditional Chinese Medicine. Block randomization will be used, and the block size will be unknown to the principal investigator (PI) and research personnel. The information of participants will be sent by an independent statistician to the center via the hospital's website. Randomization will be performed automatically under the control of a central computer system. The researcher will be able to get the random numbers and group allocation immediately in the form of an email or short message service. Participants will be randomly divided into 3 groups with the ratio of 1:1:1.

## Intervention

3

During the study, the patients are permitted to continue their regular medications including lipid-lowering drugs, antihypertensive drugs and drugs not related to the treatment of bladder dysfunction, but no use of the sympathomimetic drugs uracholine or receptor α blockers.

Patients in the 3 groups will receive different treatments of acupuncture and same basic western medicine. Both the acupuncture intervention and western medicine treatment will be given twice a week for 12 weeks, and the follow-up period will be 24 weeks. In each treatment session, every patient will be placed in a separate and quiet space. All the patients will be in prone position and wear an eye-patch. Before all the intervention, the patients’ skin will be disinfected, then the experienced acupuncturist who also be a registered practitioner will begin the treatment.

### Group A

3.1

Patients in group A only receive basic western medicine (BWM) treatment: 0.9% normal saline (NS) 250 ml + Alpha-lipoic acid (ALA) 600 mg, ivgtt; Methylcobalamin (MC) 0.5 mg, iv; Qd, twice a week for 12 weeks, 24 sessions in total.

### Group B

3.2

Patients in group B will receive EA with basic western medicine treatment. Pursuant to the traditional Chinese medicine theory, previous relevant studies and the research group acupuncture experts's opinion, the following acupuncture acupoints will be selected (bilateral): BL23 (Shenshu), BL32 (Ciliao), BL33 (Zhongliao), BL35 (Huiyang). Huatuo brand disposable and sterile 0.30 × 75 mm acupuncture needles were used. Following needle insertion, quickly and evenly lift, thrust and rotate the needle to make the patient reports electric shock sensations radiate to the perineum (Deqi sensation). According to the study of EA involving lumbosacral region on stress urinary incontinence,^[12]^ the needles on bilateral BL33 and BL35 will be connected to the acupoint nerve stimulator (SDZ-V; Huatuo Medical Technology Co., Ltd. Suzhou, China), using continuous wave type, with a frequency of 25 HZ, and a current intensity of 1 to 10 mA, resulting in contraction of superficial muscles, which was tolerated by the patients. The EA stimulation lasted for 30 minutes. Participants received 2 treatment sessions per week for 12 weeks, 24 sessions in total. The BWM treatment is the same as group A.

The methods and acupoints for acupuncture intervention are shown in Table 2.

**Table 2 T2:**
[figure not shown]
Acupuncture method.

### Group C

3.3

Patients in group C will receive sham EA with basic western medicine treatment. We use a placebo acupuncture needle that can simulate the acupuncture process and do not penetrate the skin.^[16]^ When the tip of the placebo needle touches the skin, the patient will feel tingling. However, the needle retracts inside the handle and looks shortened as if inserted into the skin.^[17]^ The shame acupoints are as follows: (1)Sham BL 23: BL23 horizontal 1 cun (≈20 mm). (2)Sham BL32: BL32 horizontal 1 cun. (3)Sham BL33: BL33 horizontal 1 cun. (4)Sham BL35: BL35 horizontal 1 cun. Similarly, the acupoint nerve stimulator will be connected to the sham BL33 and sham BL35 (bilateral), without an electricity output for 30 minutes. The BWM treatment is the same as group A.

The location of acupoints for the EA and Sham EA Groups are shown in Figure 2.

**Figure 2 F2:**
[figure not shown]
Location of acupoints for the electroacupuncture and sham electroacupuncture groups.

## Outcomes

4

### Primary outcome

4.1

The 72h-BD is a practicable, reliable and effective tool to evaluate the neurogenic bladder related lower urinary tract symptoms.^[18]^ The 72h-BD, which records the frequency of urination, the time of micturition and the urgency of incontinence for 3 days. According to the previous study on this scale to assess bladder-related dysfunction, the frequency of urinary incontinence episodes was selected as the main outcome measurement.^[19]^ The validity of 72h-BD has been validated in patients by the previous clinical studies, and as a non-invasive assessment method, the Chinese version of the scale was verified to be safe and risk-free.^[12]^

### Secondary outcomes

4.2

#### American urological association symptom index (AUA-SI)

4.2.1

The American Urological Association Symptom Index (AUA-SI) is a commonly used screening tools assess the overall severity of urinary system disease in patients.^[20,21]^ Clinical studies have confirmed the application value of AUA-SI in DNB-related research and recommend this scale to verify the effectiveness of DNB treatment.^[7,22]^ The AUA-SI contains 7 entries including 4 bladder voiding symptoms (incomplete emptying, weak stream, abdominal straining, and intermittency) and 3 bladder storage symptoms (frequency, urgency, and nocturia). Depending on the frequency of symptoms, each symptom score ranges from 0 (not at all) to 5 (almost always), for a total of 35 points. According to the total score of symptoms, it can be further divided into voiding symptoms score (incomplete emptying + weak stream + intermittency + straining) and storage symptom score (frequency + nocturia + urgency). Importantly, the 8th question of AUA-SI (“If you were to spend the rest of your life with your urinary condition just the way it is now, how would you feel about that? Answer ranging from 0 “delighted” to 6 “terrible”) was used as an overall assessment of a patient's bother regarding their urinary tract condition.^[23]^

#### Post-void residual urine volume (PVR)

4.2.2

PVR is the amount of urine retained in the bladder after a voluntary void and functions as a non-invasive diagnostic means to assess the stage of neurogenic bladder.^[24]^ The ultrasound (conventional or real-time) is used to visualize the bladder directly. It measures the bladder's volume using the ultrasound machine's internal volume calculations. Related research demonstrate high accuracy of post-void residual using transabdominal ultrasound with automated measurement of bladder volume.^[25]^ The PVR have been used to examine the urinary retention of many conditions including bladder dysfunction and infection/medication induced neurological disease.

#### Urodynamic study

4.2.3

Urodynamic tests are used to measure the bladder pressure and urine flow rate in order to estimate the neuromuscular function and dysfunction of the urinary tract, and identify the cause of bladder dysfunction. Urodynamics are commonly used in the diagnosis of stress urinary incontinence, overactive bladder syndrome, neurogenic bladder dysfunction.^[26]^ The urodynamic test is important in planning therapy of DNB, a growing number of researchers reported that urodynamics was well tolerated, most researches recommend urodynamics as the choice of DNB study.^[27,28]^ The multi-channel urodynamics is used to determine bladder capacity, contractility, compliance, sensation, and voiding dynamics. The intravesical pressure (Pves), the abdominal pressure to the bladder wall (Pabd) and the detrusor pressure (Pdet), Volume at first desire to void (mL), volume at maximal bladder capacity (mL), maximal urinary flow rate (mL/s), opening pressure (cmH_2_O), opening time (seconds) were measured. And the criterion of urodynamic diagnoses used in this trial follow the criteria recommended by the International Continence Society standardization sub-committee.^[29]^

### Adverse events

4.3

Acupuncture is generally considered to be a safe treatment.^[30]^ However, any discomfort or symptoms will be assessed. All details of adverse events will be recorded in the case report forms during the trial. The research personnel will interview patients and complete the adverse event report after the treatment. The DSMB and ethics committee will assess any correlation between the adverse event and the intervention, and make a decision on whether the study should proceed. All treatment related adverse are recorded and compared among groups for the purpose of analyzing the safety of EA treatment.

### Credibility of treatment rating scale (CTRS)

4.4

The credibility of treatment rating scale (CTRS) is a quick and easy to manage scale for measuring treatment expectancy and assessing the rationale credibility of the acupuncture intervention.^[31,32]^ It consists of 4 parts, including the patient's “perceived logic of the treatment,” “confidence in recommending the treatment to their friends who have similar complaints,” and “confidence in the treatment to relieve their complaint,” to derives the 2 predicted factors (cognitively based credibility and relatively more affectively based expectancy). The lower the total score, the greater the confidence in the treatment.

### Assessment of blinding

4.5

After the treatment session in weeks 12, the patients will be asked to fill in a questionnaire (Table 3). The percentage of patients from each group who believe that they received a true acupuncture treatment will be the principal standard for measuring the subject blinding success rate. We will analyze the difference in the patients blinding success rates among groups.

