**Method/design::**

This is a sham-controlled, patient-blinded, pioneer randomized controlled trial (RCT). One hundred fifty eligible patients will be randomly divided into 3 groups: A. basic western medicine (BWC), B. EA with BWC, C. sham EA with BWC. EA treatment will be given twice a week for 12 weeks at bilateral BL23, BL32, BL33, and BL35. The BWC group will received Alpha-lipoic acid (ALA) and methylcobalamin (MC) treatment for 12 weeks, 2 treatment sessions per week. The primary outcome is scored by the 72-hour bladder diary (72h-BD). The secondary outcomes will be scored by the American Urological Association symptom index (AUA-SI), Post-void residual urine volume (PVR) and urodynamic tests. All the assessments will be conducted at baseline and the 12th weeks after the intervention starts. The follow-up assessments will be performed with 72h-BD and AUA-SI in the 4th, 12th, and 24th weeks after intervention ends.

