### Recruitment

2.4

Participants of the study will be recruited through the outpatient clinic or inpatient, hospital-based Wechat advertising, and posters in Hospital of Chengdu University of Traditional Chinese Medicine in Chengdu, Sichuan Province, China. Any patients who are interested will be screened by telephone or on site and consented for the study. After being informed of the details of this research, participants will be asked to signed informed consent, and deliver it to an independent research assistant. Based on the Western medicine treatment, all participants will receive 12 weeks treatment with acupuncture or sham acupuncture and a series of assessments on bladder dysfunction free of charge.

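### The blinding comparison is not limited to EA versus sham, so group A, which gets no needling and cannot be patient-blinded, would very likely drive its result

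*Protocol article*

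**What the plan says.** **Who is needled.** Section 3.1 says "Patients in group A only receive basic western medicine (BWM) treatment" and lists two drugs, with no needle, placebo needle or stimulator. The abstract and section 2.3 agree, describing one arm as basic treatment. The placebo needle appears only in section 3.3: "Patients in group C will receive sham EA with basic western medicine treatment".

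Two other places say something different. Section 2.4 states that "all participants will receive 12 weeks treatment with acupuncture or sham acupuncture", and the lead-in to section 3 says "Patients in the 3 groups will receive different treatments of acupuncture and same basic western medicine".

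**What is called blinded.** The abstract calls the trial patient-blinded and section 2.3 calls it single-blind. Neither excepts group A. Section 3 adds a masking step for everyone: "All the patients will be in prone position and wear an eye-patch".

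**How blinding is checked.** Section 4.5 gives a questionnaire after the week 12 session. "The percentage of patients from each group who believe that they received a true acupuncture treatment will be the principal standard" for judging success, and then "We will analyze the difference in the patients blinding success rates among groups". Nothing limits either statement to groups B and C.

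**The concern.** In this trial a blinding check has one job: to show whether EA and sham patients could tell which they were given. EA versus sham is the first objective in the Introduction, and the primary outcome (section 4.1) is incontinence episodes that patients record in their own diary. A reader needs this check to interpret that contrast.

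Group A has nothing to be blinded to. Section 3.3 relies on the tingling felt when the placebo needle tip touches the skin, and section 3.2 on a needling sensation reported by the patient. Group A has neither over 24 sessions, and lying prone with an eye-patch does not supply it. On the section 4.5 definition group A would score a very low blinding success rate although no masking was attempted. If A is part of the comparison, the expected finding is a difference among groups, and it could be misread as a failed sham.

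**Working it through.** The article gives no figure for the blinding comparison, so there is none to reproduce. The check asks how a three-group comparison behaves when the sham works and when it does not.

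**Inputs from the article.** 50 per group, 1:1:1, with 20% dropout (section 2.7), hence 50 × (1 − 0.20) = 40 completers per group. Two-sided 0.05 (section 4.6).

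**Assumptions.** The article states no belief rates. The range used is 0–20% in A and 20–90% in B and C. It names no test either; a Pearson chi-square is used as the ordinary choice for comparing percentages.

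**Worked example, perfect sham, 40 per group.** Suppose 0 of 40 in A and 28 of 40 (70%) in each of B and C believe they had true acupuncture.
- Total believing: 56 of 120. Expected per group: 56/3 = 18.67 believing and 21.33 not.
- Deviations: −18.67, +9.33, +9.33. Sum of squares: 348.44 + 87.11 + 87.11 = 522.67.
- Chi-square = 522.67/18.67 + 522.67/21.33 = 28.0 + 24.5 = 52.5 on 2 df. P = exp(−52.5/2) = 4.0 × 10⁻¹².

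With 20 of 40 (50%) in each of B and C, expected counts are 13.33 and 26.67 and the sum of squares is 266.67. Chi-square = 20.0 + 10.0 = 30.0, P = exp(−15) = 3.1 × 10⁻⁷.

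In both cases B and C are identical, so group A alone produces the result.

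**Simulation, 20,000 trials per scenario.** Share of trials significant at 0.05:

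| Belief in A | Belief in B / C | Three-group test, n = 40 / 50 | B vs C test, n = 40 / 50 |
|---|---|---|---|
| 0–5% | equal, 50–90% | 99.98–100% | about 5–6% |
| 10% | equal, 50% | 99.4% / 99.9% | 5.5% / 5.9% |
| 20% | equal, 50% | 84% / 92% | 5.7% / 5.6% |
| 5% | equal, 20% | 51% / 64% | 5.1% / 5.1% |
| 10% | equal, 20% | 21% / 26% | 5.0% / 5.4% |
| 5% | 80% / 50% | 100% / 100% | 82% / 90% |
| 5% | 80% / 30% | 100% / 100% | 99.8% / 99.98% |

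The first five rows are a sham that works and the last two a sham that fails. With belief in B and C at 50% or more and A at 10% or less, the three-group test is significant at least 99% of the time in either case. The B versus C test stays near its nominal 5% when the sham works and responds when it fails.

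**Why an interval is needed as well.** For B versus C at 70% each, the standard error of the difference is √(2 × 0.7 × 0.3/40) = 0.102, so the 95% CI is about ±20 percentage points (±18 with 50 per group). A non-significant result would not by itself show that blinding held.

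**The case against.** The strongest reply is that section 4.5 names no test. It does not say that all three groups enter one hypothesis, Table 3 is not shown, and pairwise B versus C comparisons could follow in an analysis plan. This stands as a caution. But each group and among groups, in a three-arm trial, most naturally include group A, and the article fixes both the measure and the comparison in a section of its own. Limiting the statement to B and C belongs there.

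A reader might infer several stronger points that the documents do not support:
- *The plan cannot show whether the sham worked.* It reports a percentage for each group, so B and C can be read side by side. The among-group result is what misinforms.
- *A difference is certain.* It is not: with 10% belief in A and 20% in B and C, the three-group test is significant in only 21–26% of trials.
- *Group A patients are misled, and so drop out or under-report.* Section 2.4 is article narrative. It also says participants are informed of the details, and the consent form is not shown. No such bias can be shown from the text.
- *Week 12 is the wrong time to ask.* Perceived benefit may colour a late answer, but asking after the full course is a defensible choice. Section 4.4 also provides a credibility scale, whose schedule would be in a table that is not shown.

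**Conclusion.** The point holds in a limited form. Group A, as section 3.1 describes it, cannot be patient-blinded to acupuncture. Two passages describe its treatment inconsistently with that section, the blinding label has no exception, and the blinding comparison is not confined to the contrast where blinding is possible.

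On the natural three-group reading, the comparison would very likely show a difference even with a perfect sham, so its result says little about EA versus sham. The size rests on assumed belief rates: close to 100% of trials if belief is 0–5% in A and 50–90% in B and C, and materially less if belief in B and C is about 20%. It also rests on an ordinary chi-square test that the article does not itself specify.

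The primary estimate is unaffected. What is affected is the evidence offered in support of the sham-controlled contrast.

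**What to change.** 1. In section 4.5, restrict the blinding analysis to groups B and C. Report the difference in the percentage believing they had true acupuncture with its 95% CI; a blinding index per arm is an optional addition.
2. In the abstract and section 2.3, state that patient blinding applies to B versus C and that any comparison with A is open-label to patients.
3. Reconcile sections 2.4 and 3 with section 3.1, so that all passages agree on which groups receive real, sham or no acupuncture.
4. Optionally, give the same questionnaire once early in treatment and keep week 12 as planned.

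Items 1 to 3 are wording changes that leave the sample size, visits and data collected unchanged. Item 4 would add a few minutes per patient in B and C.

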Although the increasing incidence of DNB in the Asia-pacific region, but there is no reliable and effective treatment. Therefore, most of the treatment programs of DNB are conservative intervention, nutritional nerve antioxidant to reduce residual urine volume and prevent upper urinary tract injury, while this basic western medicine (BWM) treatment cannot achieve satisfactory effect. The reason for this is that the rehabilitation and reconstruction of bladder function requires long-term intervention, while patients with DNB are usually discharged after acute phase and in early rehabilitation. They usually lack long-lasting interventions, which may lead to a series of complications such as urinary tract infection, urinary injury, and kidney damage. Therefore, longterm, safe and effective treatment has become an urgent need for DNB patients.

Traditional Chinese acupuncture therapy has been successfully used to treat nervous system diseases for thousands of years.^[8]^ In fact, some research on acupuncture for bladder dysfunction has revealed its advantages,^[9–11]^ include relieving symptoms, improving patient quality of life, and delaying the progression of neurogenic bladder dysfunction. Electroacupuncture (EA) has been found to improve chronic urinary retention, decrease urine leakage.^[12,13]^ we believe that EA might be an effective treatment for option for DNB. Besides, it is still unknown whether the combination of acupuncture and BWM therapies could optimize the therapeutic effect. The aim for this randomized controlled trial (RCT) is to clarify the therapeutic effect of acupuncture combined with BWC for DNB.

The purpose of this study is as follows: The first objective of this study is to determine whether EA is effective as compared to a sham EA control on DNB. The second aim for this RCT is to clarify the therapeutic effect of acupuncture combined with BWC for DNB. The findings of this trial will be shared through publication and will provide useful information in forming an optimal acupuncture treatment protocol for DNB.

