### Sample size

2.7

The calculation of the sample size in this trial was based on the study about acupuncture treatment for overactive bladder with urge incontinence.^[15]^ Referring to the study, the designer recruited 85 patients and randomly divided into the acupuncture and placebo acupuncture group. And also used frequency of incontinence episodes from the 72h-BD as the main assessment indicator. To detect a clinically meaningful effect of 30% difference between the acupuncture and placebo acupuncture group, 41 cases will be needed in each group. Under the assumption of a significant level of 0.05, 80% power, and 20% dropout rate, a total of 150 participants should be recruited for this RCT (50 participants in each group with 1:1:1 allocation).

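### The blinding check compares belief in true acupuncture across all three groups, although only Groups B and C have any acupuncture masking to assess

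*Protocol article*

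**What the plan says.** Section 4.5 (Assessment of blinding) has patients complete a questionnaire after treatment in week 12. It fixes the measure: "The percentage of patients from each group who believe that they received a true acupuncture treatment will be the principal standard" for the blinding success rate. It then fixes the comparison: "We will analyze the difference in the patients blinding success rates among groups".

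The trial has three arms. Section 2.8 states: "Participants will be randomly divided into 3 groups with the ratio of 1:1:1". The arm descriptions are:

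- Section 3.1: "Patients in group A only receive basic western medicine (BWM) treatment".
- Section 3.2: "Patients in group B will receive EA with basic western medicine treatment".
- Section 3.3: "Patients in group C will receive sham EA with basic western medicine treatment".

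The masked contrast is EA against sham EA, which is also the leading aim in the Introduction: "The first objective of this study is to determine whether EA is effective as compared to a sham EA control on DNB".

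Two other places describe Group A differently. Section 2.4 (Recruitment) implies that every participant has acupuncture or sham on top of the drugs. The opening of section 3 (Intervention) implies that all three groups have some form of acupuncture.

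**The concern.** A blinding check should show whether patients given EA and patients given sham could tell which they had. Under section 3.1, Group A has neither needles nor a sham. Few of its patients should report true acupuncture, and that low figure says nothing about how convincing the sham is. A comparison across all groups therefore mixes two questions: whether drug-only patients differ from needled patients, and whether EA and sham look alike. The first will dominate.

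The label is a separate matter. In Group C, believing that the acupuncture was real is the masked answer. In Group B it is a correct guess, so a fully unblinded Group B would be reported as 100% blinding success.

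The trial is single-blind and its primary outcome comes from a patient-kept diary. Readers will look to this check when they judge the EA versus sham result. A reported difference in blinding success among groups could be taken as a failure of the sham when it reflects only the presence of Group A.

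**Working it through.** **The plan's own figure.** Section 4.5 gives none, so there is nothing to reproduce. The check asks what the stated comparison would show if masking were perfect.

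**Inputs from the article.** Section 2.7 (Sample size): "a total of 150 participants should be recruited for this RCT (50 participants in each group with 1:1:1 allocation". The same section gives 41 needed per group, a significance level of 0.05 and 20% dropout. With that dropout, 50 × (1 − 0.20) = 40 patients per group would answer. Section 4.6 makes tests two-sided.

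**Assumptions.** The article gives no belief rates. Perfect masking is represented by equal true belief rates in B and C, from 50% to 90%. Belief in Group A is varied from 0% to 30%. The article names no test, so a Pearson chi-square is used for illustration.

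**Formula.** With x_g believers out of n in each of k groups and pooled proportion p̄:

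X² = Σ(x_g − n·p̄)² / [n·p̄·(1 − p̄)], on k − 1 degrees of freedom.

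**Worked table, n = 50, A = 0/50, B = C = 35/50.**

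- p̄ = 70/150 = 0.467, so n·p̄ = 23.33 and n·p̄·(1 − p̄) = 12.44.
- The numerator is 23.33² + 2 × 11.67² = 544.4 + 272.2 = 816.7.
- X² = 816.7 / 12.44 = 65.6, p = 5.6 × 10⁻¹⁵.
- B and C are identical in this table, so all of the signal comes from Group A.

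With B = C = 25/50 and A = 0/50, X² = 37.5 and p = 7 × 10⁻⁹.

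**Simulation, 20,000 trials per setting.** Percentage of trials in which the three-group test is significant although B and C have the same true belief rate:

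| n per group | Belief in B and C | A = 0% | A = 10% | A = 20% | A = 30% |
|---|---|---|---|---|---|
| 40 | 50% | 100 | 99.3 | 85.0 | 46.2 |
| 40 | 70% | 100 | 100 | >99.9 | 97.7 |
| 40 | 90% | 100 | 100 | 100 | 100 |
| 50 | 50% | 100 | 99.9 | 92.3 | 55.1 |
| 50 | 70% | 100 | 100 | 100 | 99.4 |
| 50 | 90% | 100 | 100 | 100 | 100 |

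Results at n = 41 are close to those at n = 40.

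**B versus C only.** Under the same perfect masking, the two-group test is significant in 4.5% to 6.1% of trials, which is about the nominal 5%. If masking really fails (assumed 90% belief in B, 50% in C, n = 50), it is significant in 99.6%. With A at 0%, the three-group test is significant in 100% of trials both under that failure and under perfect masking, so its result does not separate the two cases.

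**The label.** If B is fully unblinded and C knows it had sham, belief is 100% against 0%, and a B versus C comparison shows it. If masking holds, belief is equal. The percentage therefore works as a contrast between B and C. Only the word success is wrong for Group B.

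**The case against.** The strongest reply is that the article never specifies a three-group test. Section 4.5 names no test, table or P-value rule, and section 4.6 assigns its model to the primary and secondary outcomes only. The questionnaire (Table 3) is not visible and may be meant for needled patients or include a no-acupuncture option. Objectives 1 and 2 frame the comparisons as EA against sham, so B versus C is a plausible intention. All belief rates above are assumed, and at 30% belief in Group A the false signal can fall to about half.

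This stands as far as it goes: the rejection rates describe an illustrative chi-square test, not one the article has chosen. It does not remove the point. The measure is taken from each group and compared among groups in a three-arm trial, and nothing narrows it to B and C.

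Three stronger readings are tempting, and the article does not support them:

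- *The check cannot tell intact from broken blinding.* The percentages for B and C will be available and can be compared directly. Only the overall comparison misleads.
- *Counting belief as success in Group B helps to create the false signal.* It does not. The signal comes from including Group A.
- *A non-significant B versus C result would be taken as proof of masking.* The article states no such rule.

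**Conclusion.** The point holds in a limited form. Followed as written, the comparison among groups would usually show a difference caused by the unmasked arm: about 99% or more of trials if Group A belief is 0 to 10%, about 85% or more at 20%, and about half at 30% with 50% belief in B and C. This rests on assumed belief rates, 40 to 50 answers per group, an overall chi-square test and the description of Group A in section 3.1. If the accounts in section 2.4 and the opening of section 3 were the operative ones, the premise about Group A would have to be revisited.

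The success label in Group B is a separate fault of wording. The check is ancillary: it feeds no efficacy estimate, and the same data can be read correctly afterwards through B and C alone. It still deserves correction before results are reported.

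**What to change.** In section 4.5:

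1. Limit the blinding comparison to Group B versus Group C and drop Group A from it.
2. Report the B minus C difference in the percentage believing they had true acupuncture, with a 95% confidence interval. At 70% belief in both arms the half-width is 1.96 × √(2 × 0.7 × 0.3 / n), which is 0.20 for n = 40 and 0.18 for n = 50, so the interval will be fairly wide and should be shown.
3. Report the distribution of guesses in each of the two arms. A blinding index is an optional addition.
4. Do not describe belief in Group B as blinding success. Call it the percentage believing they had true acupuncture.

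Reconcile section 2.4 and the opening of section 3 with section 3.1 on whether Group A has any acupuncture or sham.

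The cost is a few sentences and one small table. No new data are needed, and sample size and efficacy analyses are unaffected.
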